## Methods

### Study design

This is a pragmatic, parallel, cluster-randomized, controlled, superiority trial comparing a home-based versus a facility-based care delivery model for contact management. Clinics were randomized in a 1:1 ratio to conduct either home-based (intervention) or facility-based (standard of care) contact management. Randomization was stratified by country, local geography, and TB notifications. Given that the intervention is carried out by a clinic in its entirety, neither the patient, provider/outcome assessor nor the study team including data analysts will be masked to the study procedure.

Routine program data will be collected by healthcare workers and abstracted by the study team retrospectively. Prior to trial implementation, a standardized child contact management form will be implemented in both settings to standardize data collection by all facilities in both arms. The tool was adapted from a previous trial by each country team and in conjunction with the parent IMPAACT4TB project [6, 20, 21]. Children will be evaluated monthly until they complete TPT, as per the Ethiopian and South African National Guidelines. Concomitant interviews will not be prohibited.

### Study setting

This study will be conducted over 12 months in two sub-Saharan African settings with high-TB burdens: Ethiopia and South Africa. Both countries have decentralized TB services available at the local clinic. Neither country’s community-health teams currently conduct child contact management at the community-level. The schedule of the study is presented in Fig. 1.

**Fig. 1 Fig1:**
[figure not shown]
SPIRIT study schedule

In Ethiopia, each health facility is associated with 3–5 health posts in the community that serve 3–5000 persons in the community and are staffed by health extension workers. Health extension workers are community health workers who receive at least 18 months of comprehensive training and weekly supportive supervision from facility-based healthcare workers. The health extension workers diagnose and treat children with malaria, pneumonia, neonatal sepsis, and diarrhea with dehydration, provide childhood immunizations, perform mass TB screening, and provide directly observed treatment for TB index patients. In Ethiopia, HIV only partially drives the TB epidemic where only 5% of TB patients are living with HIV [2].

In South Africa, the Ward-Based Outreach Team (WBOT) system is used to provide home-based services [22]. The team includes a professional nurse or outreach team leader (OTL) and several community health workers assigned to different sections of the township. Community health workers provide TB screening and directly observed therapy. OTLs evaluate patients and initiate treatment. Contact management and referral is variably implemented at the home level. For the purposes of the study, implementation and research needs were balanced by hiring a research nurse who functioned as an OTL because health system nurses are not allowed to participate in research activities. Unlike Ethiopia, South Africa has high rates of co-infection where 58% of TB index patients are also living with HIV in 2019 [23].

### Study population

The study will attempt to enroll all close child contacts of individuals diagnosed and treated for infectious drug-sensitive TB in the study clinics. Good Clinical Practice (GCP)-trained study and clinic staff will enroll participants. Eligibility criteria for index patients and child contacts are pragmatically designed to align with the Ethiopian and South African National Guidelines regarding TPT eligibility. We will enroll index participants with pulmonary TB disease who (1) are 18 years and older, (2) attend a study clinic for TB care and live in the catchment area of that clinic, (3) are willing to have a home visit and disclose their TB diagnosis to household members, and (4) who provide informed consent. In South Africa, all index patients will need bacteriologic confirmation of pulmonary TB disease by smear, Xpert, and/or liquid mycobacterial culture. In Ethiopia, index patients may have bacteriologic confirmation or clinical diagnosis. Index patients in both countries will be excluded if there is evidence of rifampin and/or isoniazid resistance on Xpert or drug sensitivity testing from isolates identified on culture (late exclusion) or if the household has more than one index patient and whose child contacts have already participated in the study. Child contacts will be enrolled if (1) they are less than 15 years of age in Ethiopia or less than 5 years of age in South Africa, (2) they are a close contact of the index patient, and (3) their parent or legal guardian is willing to provide informed consent. Additionally, in Ethiopia, children 12 years and older must be willing to provide assent. Child contacts in both countries will be excluded if any index patient in their household has drug-resistant TB by either Xpert or drug sensitivity testing. Eligibility criteria will be adapted as country guidelines are updated.

### Cluster selection and randomization

The clinics chosen in both Ethiopia and South Africa are representative of typical clinics in their respective settings in terms of clinic size, catchment population, HIV co-infection, and provision of TB preventive treatment (Supplementary File 1). TPT initiation is poor in both countries, reaching an estimated 33% and 56% of contacts less than 5 years of age in Ethiopia and South Africa respectively in 2019 [23]. Both countries are part of the IMPAACT4TB project and were rolling out 3HP and/or 3RH for household child contacts [20].

The unblinded study statistician conducted constrained randomization balancing on baseline characteristics of the clinics that we believed would be associated with the primary outcome, including clinic geography and typical TB notifications [24]. We used STATA’s *cvcrand*function with the default balance metric which is the absolute value of the sum of the weighted differences in mean levels of covariates between the intervention and control arms [25, 26]. We assumed equal weights for all the covariates. In South Africa, the available characteristics were urban/rural stratification, sub-district and the number of TB diagnoses in the clinic averaged between 2019 and 2020 (an average was taken to account for anticipated recovery in TB notifications in 2021 after COVID-related lockdowns). Four of the clinics had much higher rates of TB diagnosis relative to the other 14 and we therefore created a size stratification so that these four clinics were placed in their own stratum. We ran *cvcrand* to generate up to 50,000 possible randomization sequences. In constrained randomization of clusters, one ought to not only consider balance on baseline covariates, but also *validity*of the set of acceptable randomization sequences from which a final one is selected [24]. The concept of validity implies that all possible pairs of clusters should be assigned to the same arm roughly 50% of the time among the sequences in the acceptable subset [24]. Too much deviation from this has a potential to inflate the Type 1 error rate. The subset of generated sequences with the lowest 25% of the balance metric values was considered a good tradeoff between reasonable covariate balance and validity. Our validity check within *cvcrand* showed that in this subset, the median proportion of times any two clinics were assigned the same study arm was 49% (min 27%, max 52%), which we considered acceptable. This subset of allocation sequences was presented at a public ceremony with representatives from participating clinics and other stakeholders. The ceremony was held within days of staff training and study initiation. Volunteers among attendees participated in drawing the final allocation sequence, and then participating clinics were informed of their study arm allocations. After clinic randomization, but before study initiation, it was found that one of the clinics in the control arm in South Africa did not directly provide TPT initiation services to children. A replacement with another facility with similar baseline characteristics and in the same geographical area was made.

In Ethiopia, data on 2020 TB notifications per clinic and region (Central, East, and South) were available to balance study arm allocations. The COVID pandemic did not significantly affect TB notifications in Ethiopia and TB notification data were therefore not averaged over time [2, 27]. We followed the same default *cvcrand* options as for South Africa. The randomization resulted in equal numbers of each region represented in each arm, and similar mean numbers of TB notifications (31 vs 33). In the subset of generated randomization sequences having the lowest 25% balance metric values, the median proportion of times any two clinics were assigned the same study arm was 43% (min 31%, max 60%). We considered this satisfactory validity, and the final sequence was randomly selected among these, and this selection was made by default within *cvcrand.* This sequence was sent to the coordinating center and site data managers. The study staff and other stakeholders in participating clinics were informed of the arm allocations in time to finalize trainings and initiate the study.

### Study description and procedures

#### Intervention arm

In the intervention arm, child TB contact management, including contact tracing, child evaluation, and TPT initiation and follow-up, will take place in the community at the child’s home (Fig. 2). Newly diagnosed eligible TB index patients will be asked to give consent to a home visit. The initial home visit will include TB symptom screening for all TPT-eligible children (< 15 years in Ethiopia and < 5 years in South Africa), and either TPT initiation for asymptomatic child contacts or clinic referral for all symptomatic child contacts. TB screening and TPT initiation will be conducted by either a research nurse (South Africa) or health extension worker (Ethiopia) in the home. Children who screen negative (0 of 8 symptoms present, see the “ TB screening and evaluation” section) will be initiated on TPT. Children who screen positive (any one symptom is present) will be counseled and referred to the local clinic for evaluation as per the local standard of care. The community health team (in Ethiopia) or the research nurse (in South Africa) will revisit the household monthly for three months to ensure linkage to care.

**Fig. 2 Fig2:**
[figure not shown]
Integrated community-based TB prevention for household eligible child TB contacts. 3HP is 12 weekly doses of rifapentine and isoniazid; 3RH is 3 months of daily rifampicin and isoniazid

In Ethiopia, drug dispensing will occur in a two-step process where the health extension worker will first screen the child in the home and then return with a one-month supply of the appropriate TPT regimen and dose after discussion with the TB focal person at the clinic (task-shared). In South Africa, the anticipated TPT regimen based on reported contacts will be brought to the household by the nurse during the initial evaluation visit. If the child is symptomatic and not initiated on TPT, the stock will be returned to the clinic pharmacy. In both countries, the child will be weighed at their initial home visit. This weight will determine the dose for the 3-month duration of TPT. In Ethiopia, the full 3-month kit of TPT will be stored at the health post for each child to prevent stockouts from affecting individuals in the middle of their TPT course.

In South Africa, HIV testing will be offered and conducted in the household for all children 18 months and older with a rapid HIV test. Children under 18 months old will be assessed for HIV exposure by both self-report and evaluation of their health card. The care relating to prevention of mother-to-child transmission (PMTCT) will be reviewed including maternal antiretroviral status, infant prophylaxis, and infant testing. If they are not up to date with testing or have been lost to follow-up, the community health team will refer that infant/mother pair to the clinic. In Ethiopia, HIV testing will not be offered in the home as HIV testing all child TB contacts is not the standard of care given the fairly low proportion of HIV co-infected TB patients (5.2%) [2]. Table 2 summarizes context-specific differences in the intervention between Ethiopia and South Africa.

**Table 2 Tab2:** Key design feature comparison between countries

	**Ethiopia**	**South Africa**
Study population – index patients	Clinically diagnosed and bacteriologically confirmed pulmonary TB patients	Bacteriologically confirmed pulmonary TB patients
Study population – child contacts	Children < 15 years of age	Children < 5 years of Age
TPT regimen^a^	3HP for those ^3^ 2 years 3RH for those < 2 years 6H for those on ART	3RH for those 0-5 years 6H for those on ART
Community-based care model	Health extension worker based at health post in the community	Outreach team leader (professional nurse) teamed with community health worker
TPT initiation and follow-up	Performed by health extension worker; **Task-shared** with clinic TB focal person	Performed by professional nurse; **Task-shifted** from clinic TB focal nurse to a community-based health nurse
Persons responsible for TPT initiation and follow-up during trial	Utilized health system’s TB focal persons and health extension workers	Research nurse and clinic’s TB focal person
HIV testing	Not performed at household visits	Performed at household visits

^a^3HP is 12 weekly doses of rifapentine and isoniazid; 3RH is 3 months of daily rifampicin and isoniazid; 6H is 6 months of daily isoniazid

#### Control arm

In the control clinics, child TB contact investigations and initiation of TPT will all take place at the facility (Fig. 3). Newly diagnosed infectious TB index patients will be encouraged to bring their household child contacts potentially eligible for TPT by age (< 15 years in Ethiopia and < 5 years in South Africa) to the clinic for TB screening. Community health workers may be used to identify child contacts, encourage clinic-based evaluation, and assess children who may be lost to follow-up, as is currently the standard of care. Children identified as TB contacts during routine screening in the MCH clinic may also be referred to the TB clinic for contact investigation and management. Medications will be dispensed by the TB focal person or the pharmacy, as per the standard of care within each control clinic.

**Fig. 3 Fig3:**
[figure not shown]
Facility-based TB prevention for household eligible child TB contacts. 3HP is 12 weekly doses of rifapentine and isoniazid; 3RH is 3 months of daily rifampicin and isoniazid

#### TB screening and evaluation

In both the intervention and control arms, eligible children will be clinically evaluated using the national TB screening tool. TB screening will focus on major pediatric symptoms including fever, cough of 2 weeks or more, wheezing, reduced playfulness or unusual fatigue, lethargy, visible mass in the neck, weight loss, or failure to thrive based on clinical report and/or the growth chart in the child’s medical record and immunization record (i.e., Road to Health Booklet). Ultimately the child will either be started on TPT (if TB disease is ruled out) or TB treatment.

#### Treatment follow-up and adherence

Children initiated on TPT will be followed at home (intervention) or in clinic (control) monthly for the duration of TPT. Adherence will be measured by return visits and pill counts in both groups. Children will also be re-screened for TB symptoms during each follow-up visit.

#### Household costing and time-and-motion

Within 2 weeks from the first TB screening and evaluation, research assistants will conduct a standardized survey with the child’s caregiver about costs incurred to either host the community health team (intervention arm) or to visit the health facility (control arm). In this first survey, we will also inquire about their household’s asset ownership, living conditions, and educational attainment. Upon TPT completion, a follow-up costing survey will capture estimated costs on follow-up care and management of TPT-related adverse events, including an assessment of catastrophic costs (costs totaling ≥20% of annual household income) [28].

For a subset of participants, a time-and-motion observation will be conducted by a research assistant at either the household or the health facility to capture the time the participant spends on each activity (screening, enrolment, counseling, etc.) at initiation and/or follow-up.

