Acceptability of home-based contact management to all stakeholders (CG, HEW, TBF, PM)	• Proportion of identified households who agree to a home visit • Proportion declining HIV testing (South Africa only) • Proportion of children HIV tested by the community health team • Proportion of newly diagnosed HIV-positive children who are referred to the clinic for ART initiation	• Individual in-depth interviews (CG, HEW, TBF, PM)
**Fidelity** to the home-based contact management strategy	• Proportion of children initiated on the correct TPT regimen • Proportion of children initiated on the correct TPT dose	• Individual in-depth interviews (CG, HEW, TBF, PM)
**Feasibility** of home visits for CGs and community-based health teams	• Average number household visit attempts per household • Mean and median duration of each household visit • Proportion of index patients who refuse to provide an address or who provide an invalid/incorrect address	• Individual in-depth interviews (CG, HEW, TBF, PM)
**Cost and cost effectiveness**	• Mean difference in total patient and health system costs between the intervention and control arms • Incremental cost-effectiveness ratio (ICER) where effectiveness is modeled as the number of disability adjusted life years (DLYs) averted by the intervention in comparison with the standard of care.	• Structured interviews to assess implementation costs • Time and Motion observations of TB preventive care

Stakeholders: *CG* Caregiver, *HEW* Health extension worker, *TBF* TB focal persons, *PM* Program manager

The secondary objectives of the study are to evaluate: (1) the TPT continuum of care by country, TPT regimen (3RH and 3HP), and age (< 5 and 5–14 years); (2) acceptability, feasibility, and fidelity of home-based contact management and HIV preventive services in each setting; (3) TPT treatment outcomes, including tolerability and reported adherence; and (4) the cost-effectiveness of home-based versus facility-based child contact management (Table 1).

Data will be collected on staffing changes within the TB clinic and community health teams and stockouts of TPT medications, pyridoxine, and other supplies needed for pediatric contact management (specimen collection, file and registers, etc.), to understand trends in the data.

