#### Costing and cost-effectiveness analysis

The endpoint of interest for the costing analysis will be a continuous outcome of household costs from enrolment until treatment completion/discontinuation, and health system costs through the course of the study period. We will calculate the mean difference in costs, comparing the intervention to the SOC arms.

The unit cost of diagnosis and treatment will be calculated from measured costs from the patient and health system perspectives. The outcome of interest will be the sum of patient plus health system costs, expressed as unit costs (e.g., cost per test, cost per TB treatment), under the intervention and under the standard of care. This outcome will not be subject to a formal statistical hypothesis test.

The modeled incremental cost-effectiveness ratio will be calculated from cost and effectiveness outcomes, including both patient and health system perspectives. The outcome of interest here will be the incremental cost per DALY (disability-adjusted life year) averted. This outcome will not be subject to a formal statistical hypothesis test.

All analysis will be conducted using R version 4.1.1 (R Foundation for Statistical Computing, Vienna, Austria) [37].

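### The follow-up household cost survey is tied to TPT completion, but the cost endpoint runs to completion or discontinuation, so follow-up and adverse-event costs of children who stop early are not collected

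*Protocol article*

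**What the plan says.** Under Household costing and time-and-motion, the protocol article sets two caregiver surveys. The first follows screening: "Within 2 weeks from the first TB screening and evaluation, research assistants will conduct a standardized survey". The second follows the end of a full course: "Upon TPT completion, a follow-up costing survey will capture estimated costs on follow-up care and management of TPT-related adverse events". The same sentence attaches the assessment of catastrophic costs (at least 20% of annual household income) to this second survey. No survey is named for a child who stops early, is lost to follow-up or is never screened.

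Under Costing and cost-effectiveness analysis, the endpoint is "a continuous outcome of household costs from enrolment until treatment completion/discontinuation, and health system costs through the course of the study period", and the contrast is stated directly: "We will calculate the mean difference in costs, comparing the intervention to the SOC arms". Table 1 lists it as an outcome beside the incremental cost-effectiveness ratio: "Mean difference in total patient and health system costs between the intervention and control arms".

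Under Costing and time-and-motion data, up to 400 index households are costed, and the questionnaire goes to caregivers of enrolled children. Health-system costs come from separate sources such as budgets, interviews, staff observation and timed forms.

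**The concern.** The data collection does not cover the endpoint as defined. Table 1 anticipates stopping for reasons that include toxicity, severe illness and family preference, and the analysis section defines loss to follow-up. For these children the window closes at discontinuation, but no survey is scheduled there. Their first-survey costs remain. Their costs of later visits and of managing adverse events are not asked for, and they are outside the catastrophic-cost assessment. Children who stop because of toxicity are a group in whom adverse-event costs matter, and the later analysis cannot recover answers that were never collected.

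The second issue concerns the first survey. A control child is screened mainly when the family brings the child to the clinic; in the intervention arm the team goes to the home. The families surveyed in each arm are thus selected by a step that the intervention is designed to change. The article does not say whether the mean difference is per household reached or per index household, nor how households never screened enter it.

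**Working it through.** **1. The plan's own figure.** 100 interviews × 2 arms × 2 countries = 400, as stated. The concern does not depend on the number of interviews; it depends on who is surveyed and when.

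**2. Triggers against the endpoint window.**

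| Child's course | Window closes at | First survey | Follow-up survey |
|---|---|---|---|
| Completes TPT | completion | yes | yes |
| Starts, then stops | discontinuation | yes | none named |
| Starts, then lost to follow-up | not stated separately | yes | none named |
| Never screened | no TPT course | none named | none named |

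Rows two and three are the mismatch. Row four is the denominator question.

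**3. Size of the follow-up gap (illustration; no cost figures in the documents).** Assume 1 unit per monthly visit, 3 visits for a completer, 1 for a stopper, and a share q of starters who stop early. The all-starter mean is 3(1 − q) + 1·q.

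| q | Completers only | All starters | Stoppers' follow-up cost taken as zero |
|---|---|---|---|
| 10% | 3.0 | 2.8 | 2.7 |
| 20% | 3.0 | 2.6 | 2.4 |
| 30% | 3.0 | 2.4 | 2.1 |

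A completer-only mean is 0.2 to 0.6 units too high. Counting stoppers at zero is 0.1 to 0.3 units too low. If a stopper also bears an adverse-event cost of a units, the all-starter mean becomes 3(1 − q) + q(1 + a), and the completer-only error is q(2 − a). It changes sign once a exceeds 2, so the direction is not known in advance. In the arm difference the errors cancel only if they are equal in money in both arms.

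**4. The denominator (illustration).** Let C0 and C1 be the household cost of a control and an intervention family reached, and p0 and p1 the proportions of households reached. Households never screened have zero visit cost.
- Per household reached: C1 − C0.
- Per index household: p1·C1 − p0·C0.

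Set C0 = 1.0. The difference per household reached is −0.50 if C1 = 0.5 and −0.70 if C1 = 0.3, whatever the reach. Per index household:

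| Reach, control vs intervention | C1 = 0.5 | C1 = 0.3 |
|---|---|---|
| 30% vs 60% | 0.00 | −0.12 |
| 30% vs 90% | +0.15 | −0.03 |
| 50% vs 90% | −0.05 | −0.23 |
| 80% vs 90% | −0.35 | −0.53 |
| 90% vs 90% | −0.45 | −0.63 |

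A change of sign requires p1/p0 > C0/C1: above 2 for C1 = 0.5, and above 3.33 for C1 = 0.3. The first row borrows the sample-size assumption of 30% TPT initiation, doubled by the intervention. That is initiation per child, not screening per household, and serves only as a rough proxy.

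**The case against.** The article condenses a longer protocol, and the endpoint's wording shows that early stoppers are meant to be included. On this view the survey sentence is loose shorthand for the end of TPT. That may be so, but the two sections as published disagree, and a field team following the survey section would not interview a stopper.

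On the first survey, the defence is largely right. A family that never attends has no visit to cost, so no visit-cost data are lost. A mean among users is a legitimate unit cost, and the article also reports unit costs. It never states that the mean is per index household. A per-index-household figure has a weakness of its own: it makes an arm look cheaper because children receive no care. What stands is that a listed between-arm outcome has no stated denominator while its respondents are selected by a step the intervention changes.

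A reader might go further and infer that the household saving will be overstated or have the wrong sign. The documents do not support that. They contain no cost figures and no household screening rate. Screening precedes initiation and households can hold several children, so household reach may well exceed 30%. The article also reports 2019 initiation of 33% in Ethiopia and 56% in South Africa among contacts under 5. Control clinics may use community health workers to encourage attendance, and the Limitations section expects control care to improve. Table 1's total also includes health-system costs, which do not depend on these surveys.

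**Conclusion.** The mismatch between survey trigger and endpoint window holds. As written, follow-up, adverse-event and catastrophic-cost figures come from completers, and the stated household endpoint is not fully measured in children who stop early or are lost. Under the visit-cost assumptions above, the completer-only follow-up mean is 0.2 to 0.6 units too high on a base of 3 when 10% to 30% stop; an adverse-event cost above 2 units per stopper would reverse this. It would be wrong to say that early stoppers leave the cost comparison altogether, because their first-survey costs stay in.

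The screening trigger is a secondary matter of denominator and labelling. The size and sign of the gap between the two denominators cannot be derived from the documents, and the gap shrinks as control reach approaches intervention reach.

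Both parts concern the household component of one implementation outcome. The primary endpoint is unaffected, and the article plans no formal test of the unit-cost or cost-effectiveness-ratio outcomes.

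**What to change.** 1. In Household costing and time-and-motion, trigger the follow-up survey, including its adverse-event and catastrophic-cost items, at completion, discontinuation or loss to follow-up, whichever comes first. It then matches the window in Costing and cost-effectiveness analysis. The cost is a few surveys at a different time, some of them harder to obtain: loss to follow-up is declared only after three months without a visit, so some families will be hard to reach. Report by arm how many starters have no follow-up survey.

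2. In Costing and cost-effectiveness analysis, label the mean among surveyed families as a cost per household reached. Also report the between-arm household difference per enrolled index household with an eligible child, using the recorded proportion screened and zero visit cost for households never screened. Restricting to households with an eligible child avoids counting those with no child in the age range as non-attenders. This should need no new interviews. One caution is that finding eligible children may itself differ by arm, so the source used for the denominator should be the same in both; the index patient's contact report at the clinic is one candidate.
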